### Participant recruitment, enrollment, and randomization

Participants will be recruited from the orthopedic clinics at HSS in Manhattan, New York. The target sample will be 74 patients. To enroll 74 participants, we expect to screen 500 individuals with KOA who are scheduled to undergo TKR. We will monitor recruitment success including screen failure rates, to inform the design of the planned larger study to follow this one. Patients who meet the inclusion criteria will be contacted by research staff and invited to join the study. Once a patient meets the criteria and we have obtained informed consent, they will be scheduled for their first data collection visit, either in person or virtually, with a blinded research assistant, and subsequently randomized. Block randomization will be used in REDCap to randomize participants to either the *Moving Well* arm or the *Staying Well* arm.

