### Study population and sample size

The participants of the study will be people with KOA who are 50 years of age or older, have a TKR scheduled in 8 weeks or more, speak English, have access to a computer, the internet, and a working phone. We will exclude people who are unable to exercise (wheelchair-bound or bedbound), have a history of any joint replacement surgery, or have any rheumatic disease other than KOA.

The peer coaches of *Moving Well* will be people with KOA who had a TKR at least 12 months before they initiate their training as peer coaches of the intervention. This study will have 5 peer coaches.

The sample size estimation assumed four repeated measures, a range of intra-class correlations (0.05 to 0.20) for the repeated measures, and a Bonferroni-adjusted overall type I error of 5% (after controlling for two primary outcomes). We estimate a 20% attrition rate and will recruit 93 subjects, resulting in 37 participants in each arm of the study (total of *N* = 74 completers). The trial is designed to have at least 80% power to detect a standardized effect size of d = 0.5 or 0.5 standard deviations between the intervention and attention control arms. The standardized effect size is equivalent to a 2.7-point change in the PHQ-8 score, and a 1.6-point change in the GAD-7 score.

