### Data analysis

We will use descriptive statistics, t-tests, and Chi-square tests as appropriate to compare patients in each study arm. We will assess group differences between baseline and the week before TKR, 6 weeks after TKR, and 6-, 12-, and 24-months after TKR with parametric and nonparametric analyses including one-sample t-tests, Wilcoxon rank sum, and Chi-square tests or Fisher’s exact test of proportions, as appropriate. All tests will be two-sided (unless otherwise stated) and the overall type I error will be maintained at 5%.

We will use linear and generalized linear mixed effects regression models to analyze the repeated measures of all outcomes. Although a significant treatment*time interaction will conclude rejection of the hypothesis, in this pilot study we will focus on obtaining estimates of baseline adjusted treatment effects at the end of treatment as preliminary evidence of effectiveness to power a future trial. We will correct the inflation of the type I error due to multiple primary outcomes using Holm’s stepdown procedure. Due to the exploratory nature of the secondary outcomes, we will not adjust the type I error. Our mixed models provide valid inferences when data are missing at random. However, we will also test the plausibility of this assumption and repeat our analysis using pattern-mixture models [65].

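### The recruitment section sets enrolment at 74, but the sample-size section recruits 93 to leave 74 completers; enrolling only 74 would leave about 59

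*Protocol article*

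**What the plan says.** Two sections of the protocol article give the size of the trial.

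- **Study population and sample size:** "We estimate a 20% attrition rate and will recruit 93 subjects, resulting in 37 participants in each arm of the study". The same sentence gives the total as 74 and labels these people completers. The design claim that follows is "The trial is designed to have at least 80% power to detect a standardized effect size of d = 0.5". Its stated inputs are four repeated measures, an intra-class correlation (ICC) between 0.05 and 0.20, and a 5% error rate split by Bonferroni over two primary outcomes.
- **Participant recruitment, enrollment, and randomization:** "The target sample will be 74 patients. To enroll 74 participants, we expect to screen 500 individuals with KOA". This section does not mention 93, attrition or completers. It goes on to consent, the first data collection visit and randomisation.

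**The concern.** The number 74 counts people who finish in one section and people who enter in the other. The recruitment section is the one that staff would naturally follow when deciding when to stop. Stopping at its figure removes the whole attrition allowance that the sample-size section built in.

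Three things depend on the number:

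- the count of completers and the power claimed for it;
- the precision of the treatment-effect estimates that the Data analysis section wants for powering a later trial;
- the benchmark for recruitment success. The recruitment section plans to monitor recruitment and screen failures for the larger study, and the expected yield from 500 screened differs according to whether 74 or 93 are enrolled.

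**Working it through.** **Inputs.** From Study population and sample size: 20% attrition, 93 recruited, 37 completers per arm (74 in total), d = 0.5, four repeated measures, ICC 0.05 to 0.20, and Bonferroni over two outcomes (0.05/2 = 0.025 each). From Data analysis: two-sided tests. From the recruitment section: 74 enrolled, 500 screened. Equal allocation is inferred from the 37 per arm.

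**Step 1: reproduce the recruitment number.** 74/(1 − 0.20) = 92.5, rounded up to 93. The sample-size section is consistent with itself, and 93 × 0.8 = 74.4 completers.

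**Step 2: apply the same attrition to the other target.** 74 × 0.8 = 59.2, so about 59 completers, or 29.5 per arm. The loss is 74 − 59 = 15 completers, about 20%. This step needs no model.

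**Step 3: power, under an assumed method.** The article does not give its formula. I assume a two-sample comparison of the mean of m repeated measures, in completers only. The SD of that mean, in units of the single-visit SD, is √[(1 + (m − 1)·ICC)/m]. With n per arm, the noncentrality of the t statistic is (0.5/SD factor) × √(n/2), on 2n − 2 degrees of freedom.

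At ICC 0.20:

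- m = 4: SD factor √(1.6/4) = 0.632, effective d = 0.791. Noncentrality is 3.40 at 37 per arm and 3.04 at 29.5.
- m = 3 (the 6-, 12- and 24-month visits): SD factor √(1.4/3) = 0.683, effective d = 0.732. Noncentrality is 3.15 at 37 per arm and 2.81 at 29.5.

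Power from the noncentral t distribution, two-sided 0.025:

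| Measures averaged | ICC | 37 per arm | 29.5 per arm |
|---|---|---|---|
| 4 | 0.05 | 95.5% | 89.6% |
| 4 | 0.10 | 92.8% | 85.4% |
| 4 | 0.15 | 89.8% | 81.0% |
| 4 | 0.20 | 86.4% | 76.7% |
| 3 | 0.05 | 89.4% | 80.5% |
| 3 | 0.10 | 86.4% | 76.7% |
| 3 | 0.15 | 83.4% | 72.9% |
| 3 | 0.20 | 80.3% | 69.4% |

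At 37 per arm, both variants satisfy the stated power over the whole ICC range. The three-measure variant at ICC 0.20 comes closest to the stated size: the normal approximation asks for 36 per arm. At 29.5 per arm, the four-measure variant drops below 80% only at ICC 0.20, and the three-measure variant does so from 0.10 upward.

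**Step 4: screening yield.** 74/500 = 14.8% and 93/500 = 18.6%. At a yield of 14.8%, enrolling 93 needs 500 × 93/74 ≈ 628 screened.

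**The case against.** The likeliest explanation is a labelling slip. The sample-size section states 93 and explains it, while the recruitment section offers no competing reasoning and may simply have carried over the completer count. Harm arises only if the recruitment section is followed in preference to the other. That is fair as an account of how the conflict arose, but it does not remove it. The recruitment text speaks of enrolling 74 and bases its screening forecast on that number.

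The objections to stronger readings carry more weight:

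- A reader might infer that the 80% power is lost outright. The documents do not support that. With the four measures the plan names, 59 completers still give at least 81% at ICC 0.15 and below. The formula is not stated, so every power figure here is conditional.
- A reader might quote the power of a single 6-month comparison. The sample size was not derived that way, and a single-visit comparison is already far below 80% at 37 per arm (about 45%). Most of that shortfall therefore has nothing to do with 74 versus 93.
- A reader might call 500 screened an error. It is too low only if the yield of 74 per 500 was intended. If 500 was set with 93 in mind, the implied yield is 18.6% and nothing is wrong beyond the label.
- Completer-only power is conservative. The planned mixed models use partial follow-up from people who drop out, so 74 enrolled would carry somewhat more information than 59 completers. The article does not allow the gain to be computed.

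**Conclusion.** The contradiction is real and the text is wrong as written: the enrolment number is 93 in one section and 74 in the other. The loss of about 15 completers if 74 is followed rests only on the article's own 20% attrition.

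The effect on power is narrower. Under the assumed comparison of averaged measures in completers, it falls at ICC 0.20 from about 86% to 77% (four measures) or from about 80% to 69% (three follow-ups). A claim of at least 80%, made over an ICC range, has to hold at the top of that range, so the promise is broken there. With four measures it is not broken at 0.15 or below.

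**What to change.** In the recruitment section, state that 93 participants will be enrolled and randomised to obtain 74 completers. In the same sentence, reconcile the screening forecast: give about 628 if the yield of 74 per 500 is what the team expects, or keep 500 and say that it assumes a yield of 18.6% for 93 enrolled.

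If 74 is in fact the enrolment cap, change the sample-size section instead: about 59 completers after 20% attrition, with the power restated and its method and ICC named.

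The first option is a sentence-level correction and adds no participants beyond the 93 already planned; its only possible cost is more screening. The second costs a lower stated power at the upper end of the ICC range.

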### Primary and secondary outcomes

The primary outcome will be the difference in levels of anxiety and depression 6-, 12-, and 24-months post-surgery between *Moving Well* and *Staying Well*. The GAD-7 [54] and PHQ-8 [55] will be used to assess the participants’ level of anxiety and depression respectively. Participants will complete the data collection survey at baseline, 6-, 12-, and 24-months post-surgery. If participants have not completed the data collection surveys, a blinded member of the research team will follow up with a phone call to complete the forms over the phone and minimize missing data.

Secondary outcomes will include change from baseline to 6-, 12-, and 24-months post-surgery in the level of social support, general health status, level of pain catastrophizing, knee pain and function, level of self-efficacy, level of sleep disturbance, and opioid use for knee pain. Table 4 has details of the instruments that we will be using to measure primary and secondary outcomes and the time points that data collection will occur. These secondary outcomes will be measured respectively using the following: Lubben Social Network Scale-18 (LSNS-18) [56], 12-Item Short Form Survey (SF-12) [57], Pain Catastrophizing Scale (PCS) [58], Knee Injury and Osteoarthritis Outcome Score (KOOS) Pain and Activities of Daily Living (ADL) sub-scales [59], General Self-Efficacy Scale (GSF) [60], Patient-Reported Outcomes Information System (PROMIS) Sleep Disturbance Scale [61], and participant self-report use of opioids for knee pain.

**Table 4 Tab4:** Data collection timepoints and respective outcomes

	**Baseline**	**1-week pre- surgery**	**6-weeks post- surgery**	**6-months post-surgery**	**1-year post- surgery**	**2-years post-surgery**
Sociodemographic information (collected via EHR and patient survey)	x					
Medical history (collected via EHR and patient survey)	x					
Surgical history (collected via EHR and patient survey)	x					

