**Methods:**

This is an open-label pilot randomized clinical trial that will test the feasibility and effectiveness of the *Moving Well* intervention compared to an attention control group, *Staying Well*, to reduce symptoms of anxiety and depression in patients with KOA undergoing TKR. The *Moving Well* intervention is guided by Social Cognitive Theory. During this 12-week intervention, participants will receive 7 weekly calls before surgery and 5 weekly calls after surgery from a peer coach. During these calls, participants will be coached to use principles of cognitive behavioral therapy (CBT), stress reduction techniques, and will be assigned an online exercise program, and self-monitoring activities to complete on their own time throughout the program. *Staying Well* participants will receive weekly calls of similar duration from research staff to discuss a variety of health topics unrelated to TKR, CBT, or exercise. The primary outcome is the difference in levels of anxiety and/or depression between participants in the *Moving Well* and *Staying Well* groups 6 months after TKR.

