**Secondary Outcomes – Patient-reported and/or electronic health record**						
Resources used to prepare for surgery	x	x				
KOOS pain and ADL subscales	x	x	x	x	x	x
Lubben Social Network Scale	x	x	x	x	x	x
Short Form-12	x	x	x	x	x	x
Pain Catastrophizing Scale	x	x	x	x	x	x
General Self-Efficacy Scale	x	x	x	x	x	x
Opioid use	x	x	x	x	x	x
COVID-19 screener survey	x	x	x	x		
Exercise survey	x	x	x	x	x	x
Sleep disturbance (PROMIS)	x	x	x	x	x	x
Surgical outcomes			x	x	x	x
Program Evaluation			x	x	x	x
Knee range of motion	x	x	x	x		
Blood Pressure	x	x	x	x		
Resting Heart Rate	x	x	x	x		
Weight	x	x	x	x		
Timed up and go test	x	x	x	x		
6-min walk test	x	x	x	x		
30 second chair stand test	x	x	x	x		
Quadriceps Strength using a handheld dynamometer	x	x	x	x		

*EHR* Electronic health record, *PHQ – 8* Patient Health Questionnaire 8 items, *GAD-7* Generalized Anxiety Disorder 7 items, *KOOS ADL* Knee Injury and Osteoarthritis Outcome Score Activity of Daily Living Sub-scale, *COVID-19* Coronavirus disease 2019, *PROMIS* Patient-Reported Outcomes Measurement Information System

Other secondary outcomes include the post-surgery inpatient rehabilitation duration assessed by participant self-report at 6 months post-surgery, and change in the following objectively measured physical parameters from baseline to 6 months post-surgery: knee range of motion using a goniometer, Timed Up and Go test (TUG), 6 Minute Walk Test (6MWT), 30-Second Chair Stand test, and quadriceps strength using a handheld dynamometer (only for those that did the data collection in person) [62–64]. Table 5 contains information about the measures that will be collected in the study with the corresponding time points.

**Table 5 Tab5:** Detailed measures table

Name/Construct	Type (i.e., primary, secondary, other)	Time Frame	Description / Instrument
**Patient Health Questionnaire-8 (PHQ-8)** [55]	Primary	Baseline and 6-month follow up	The PHQ-8 is an 8-item scale that screens for depression. Scores range from 0 to 24 with higher scores indicating greater severity of depression
**Generalized Anxiety Disorder Assessment (GAD-7)** [54]	Primary	Baseline and 6-month follow up	The GAD-7 is a 7 item self-reported questionnaire for screening and severity measuring of generalized anxiety disorder. Scores range from 0 to 21, with higher scores indicating greater severity of anxiety

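### The primary outcome is timed in conflicting ways and multiplicity control covers only the two scales, so the stated 5% overall error is not assured and the 80% power depends on which contrast is meant

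*Protocol article*

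**What the plan says.** The protocol article describes the primary outcome or its test in several places.

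- **Abstract, Methods:** "The primary outcome is the difference in levels of anxiety and/or depression between participants in the" two groups, timed at 6 months after knee replacement.
- **Background, last paragraph:** the hypothesis concerns anxiety and depression at 6, 12 and 24 months, against both baseline and the control group.
- **Primary and secondary outcomes:** "The primary outcome will be the difference in levels of anxiety and depression 6-, 12-, and 24-months post-surgery between" the arms.
- **Table 5:** PHQ-8 and GAD-7 are typed as primary, with time frame "Baseline and 6-month follow up".
- **Data analysis, estimation:** "we will focus on obtaining estimates of baseline adjusted treatment effects at the end of treatment", as preliminary evidence for powering a later trial.
- **Data analysis, decision:** the same sentence makes a significant treatment-by-time interaction the ground for deciding the hypothesis. The preceding paragraph lists group comparisons at five post-baseline visits.

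On error control, the sample size section assumes "a Bonferroni-adjusted overall type I error of 5% (after controlling for two primary outcomes"). The data analysis section says "We will correct the inflation of the type I error due to multiple primary outcomes using" Holm's procedure, and "All tests will be two-sided (unless otherwise stated) and the overall type I error will be maintained at 5"%. No sentence says how several visits are handled. The design claims "at least 80% power to detect a standardized effect size of d = 0.5 or 0.5 standard deviations" with 37 completers per arm.

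The abstract and the trial design section join the two scales with 'and/or'. The outcomes section joins them with 'and'.

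**The concern.** A reader cannot tell which result is the primary one. There are two candidate definitions (6 months; 6, 12 and 24 months). The estimation focus falls at neither: with five weekly calls after surgery, treatment ends about 5 weeks post-operatively, near the 6-week visit in Table 4. The decision test matches neither definition directly. An interaction asks whether the arm difference varies over time. If baseline is a covariate and only follow-up visits are modelled, a constant benefit at 6, 12 and 24 months produces no interaction at all.

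Three things are at stake. Taken literally, the outcomes section yields 2 scales × 3 visits = 6 primary comparisons, while the correction counts two. The text leaves room to select the visit once data are seen. And the stated sample size suits some of these contrasts but not others. The pilot's estimate is meant to size a larger trial, so the time it refers to needs to be fixed.

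**Working it through.** **Inputs from the document.** Overall two-sided error 5%, Bonferroni over two scales, so 0.025 each; d = 0.5; 37 completers per arm; 20% attrition; four repeated measures; intra-class correlation (ICC) 0.05–0.20.

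**Assumed.** Between-scale correlation 0–0.7; between-visit correlations above 0.20; equal correlation between all pairs of visits.

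**1. Reproducing the stated size.**

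Recruitment: 74 / (1 − 0.20) = 92.5, so 93, as stated.

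Per arm: n = 2f(2.241 + 0.842)² / d², where f is the variance of the summary in units of one visit's variance. For the mean of m visits, f = (1 + (m − 1)·ICC) / m.

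- Three follow-up visits, ICC 0.20: f = 1.40/3 = 0.467, n = 35.5, so 36. At 37 per arm, SE = √(2 × 0.467/37) = 0.159, 0.5/0.159 = 3.15, and power = Φ(3.15 − 2.24) = 81.8% (80.3% with the t distribution).
- All four measures, ICC 0.20: f = 0.40, n = 31. This meets 80% but does not lead to 37.

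The stated size therefore fits one time-averaged test per scale over three follow-up visits, at the upper end of the stated ICC range.

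**2. Power of the candidate contrasts at 37 per arm, 0.025 two-sided, d = 0.5.**

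| Contrast | f | Power, normal | Power, t |
|---|---|---|---|
| 6 months, unadjusted | 1 | 46.4% | 44.9% |
| 6 months, baseline-adjusted, correlation 0.20 | 1 − 0.04 = 0.96 | 48.1% | 46.6% |
| Mean of 6, 12, 24 months, unadjusted, ICC 0.20 | 0.467 | 81.8% | 80.3% |
| Same mean, baseline-adjusted, ICC 0.20 | 0.467 − 0.04 = 0.427 | 85.3% | 84.0% |

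For the unadjusted 6-month contrast, 80% power needs 77 per arm (n = 76.04). The effect detectable with 80% power at 37 per arm is (2.241 + 0.842) × √(2/37) = 0.72.

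At an assumed baseline correlation of 0.5 or 0.7, both outside the document's range, the baseline-adjusted 6-month power is 59.6% or 77.9%, still under 80%.

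**3. Familywise error.** Holm over two scales rejects something at a given visit exactly when the smaller p-value is below 0.025.

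- One test per scale, independent: 1 − 0.975² = 4.9%. Simulated with between-scale correlation 0–0.7: 4.3–5.0%.
- Three visits, all six tests independent: 1 − 0.975⁶ = 14.1%.
- Three visits, correlated, any hit counting (400,000 null draws per cell):

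| Visit correlation | Scale correlation 0 | 0.5 | 0.7 |
|---|---|---|---|
| 0.05 | 14.2% | 13.3% | 12.4% |
| 0.20 | 13.8% | 13.0% | 12.2% |
| 0.50 | 12.7% | 11.8% | 11.0% |
| 0.70 | 11.2% | 10.4% | 9.6% |

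The first two rows use the document's own ICC range and give about 12–14%.

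**The case against.** The strongest reply is that the article names a deciding test, the treatment-by-time interaction, which is one test per scale. Holm over two such tests keeps 5%, and so does any single fixed visit. This stands. A reader might infer from the three-visit definition that the 5% error is breached, but that needs separate tests at each visit, Holm restarted each time, and success on any hit. No sentence states that rule. The document only fails to exclude it.

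A reader might also count the end of treatment as a further primary test. The text does not support this: it is offered as a focus of estimation for planning a later trial, not as a success criterion. It still needs reconciling with the stated times.

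Table 5 is weaker evidence than it looks, because it gives the same 6-month time frame for nearly every patient-reported measure, including secondary ones that the outcomes section places at 6, 12 and 24 months. The abstract is the clear 6-month statement.

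Finally, a statistical analysis plan that is not shown may settle the matter. It may, but it cannot agree with all of these statements at once. The problem is conflicting text in the article, not detail left for later.

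**Conclusion.** The contradiction holds and should be corrected. The primary outcome has two incompatible timings, an estimation focus outside both, and a decision test that addresses neither difference directly.

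The error-rate consequence is conditional: 5% is kept with one test per scale, and rises to about 10–14% only if any of three separately tested visits may count. That range rests on the assumed correlations listed above.

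The power consequence is firmer. Within the document's ICC range, 37 per arm supports the 80% claim for a mean over three follow-up visits, which is nowhere named as primary. It does not support it for the 6-month contrast, where power is about 45–48%.

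**What to change.** Name one primary contrast per scale and use it in the abstract, the hypothesis paragraph, the sample size section, the trial design section, the outcomes section, Table 5 and the data analysis section. Apply Holm over those two tests, state that success on either scale suffices, and settle 'and' versus 'and/or' to match. Make the other visits and the end-of-treatment estimate secondary, and stop using the interaction as the deciding test unless it is the chosen contrast.

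Two choices are workable:

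- **Baseline-adjusted mean difference over 6, 12 and 24 months.** This fits the stated sample size, with at least 80% power at ICC 0.20 and 37 per arm.
- **Baseline-adjusted difference at 6 months.** This fits the abstract and Table 5, but the sample size section must then give power of about 45–48% at d = 0.5 and 0.025 two-sided, or a detectable d of about 0.72.

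The cost is wording, with no new data. The individual 12- and 24-month results lose primary status under either choice, and the stated power falls if 6 months is chosen.
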